### Study design

A mixed-methods study [23] with different methodological components will be carried out (sections A-D). The study will be led by the Institute for Social Medicine and Epidemiology of the University of Lübeck. Recruitment will take place at a community clinic in Germany (Neurological Centre, Segeberger Kliniken GmbH in Bad Segeberg). A physiotherapist at this clinic will be in charge of screening the patients for their eligibility within the first three days of their MKP and recruiting them into the study by personally addressing potential participants, giving out the information sheet and collecting the informed consent.

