During MKP, after completing an exercise, patients record the repetition rate or duration of the exercises on the tablet and rate them with regard to well-being, effort and fun. During the MKP, patients also take part in two patient-centred seminars. The first is primarily for acquiring knowledge and motivation. The focus of the second seminar is on preparing for everyday life at home. Each patient considers personal barriers that may arise in daily routine and strategies to overcome those barriers. Possible action alternatives are defined and entered into the app. At an individual appointment at the end of the MKP, patients plan their personal home training programme on the tablet, with the support of the physiotherapist. The patient chooses exercises that match their abilities, needs and preferences. The physiotherapist assists the patient in putting together their individual training programme: she gives advice regarding the selection of the activating exercises, the degree of difficulty and the number of repetitions. The exercises and the adaptation of the exercises over the weeks are based on the learning method of behaviour shaping in operant conditioning. Here, the desired motor behavioural goal is achieved by gradually increasing effort and difficulty, practising repetitive exercises and constantly adjusting the exercises to the patient’s level of ability. Shaping has proven to be an effective training method in neurological movement disorders [18]. Patients will set a date and time for at least three 30-min sessions of physiotherapy exercises and for at least one physical activity per week for the next three weeks at home. The app displays this individually scheduled training programme in a calendar function. At home, the app reminds patients through a sound signal and/or push notification to execute their exercise programme at the scheduled time. Postponing a session (e.g., due to temporary aggravation of motor impairments, so-called off periods) is possible. The videos offer visual support in the execution of the selected exercises. After completing a scheduled training session, patients will document whether the given repetition number or duration was achieved and whether there were problems performing the exercises, and they also rate the activity in terms of well-being, effort and fun. After the end of the MKP, the data are transferred automatically from the app into an administration panel called “Cockpit” at the clinic. There, the supervising physiotherapist can monitor adherence by controlling the patient’s documentation regarding the execution of the exercises and activities, the repetition number, incomplete video viewings, etc. To permit this, the app transmits the gathered statistics for the activities performed by the patients at regular intervals. To be independent of wireless Internet access, transmission takes place via the mobile network. Based on these data, the physiotherapist provides feedback by phone and adjusts the training programme at regular intervals after the end of the MKP. Because PD patients are prone to small movement amplitudes during exercise that they cannot perceive and therefore cannot correct by themselves, regular correction by experts is required. For this reason, in addition to the telephone contacts, the patients visit the clinic four times after their MKP. Travel expenses to the clinic will be financially reimbursed. If patients have any further need for assistance between those pre-defined appointments, they can contact their physiotherapist at the hospital. Regular, attentive care and feedback from the physiotherapist promote long-term adherence [19].

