## Methods

### Eligibility criteria

All patients admitted to our partner clinic for a three-week MKP with a diagnosis of idiopathic Parkinson’s syndrome will be eligible to participate (ICD G20.0 and G20.1). Concomitant care and interventions as e.g. privately organized physiotherapy sessions after the MKP are allowed.

Exclusion criteria: Montreal Cognitive Assessment (MoCA) < 18 points, Berg Balance Scale < 41 points, a major depressive episode, moderate to severe dementia, and cardiovascular and orthopaedic/surgical reasons that argue against independent home training. Participants will be also excluded from the study if they are being admitted to an acute hospital during their MKP.

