### A: quantitative measures

To examine the long-term effects, we will conduct a monocentric, quasi-randomized longitudinal study with three measurement times: at the beginning (t_0_) and end of the MKP (t_1_) and 9 months after the MKP (t_2_). Recruitment of control group (CG) and intervention group (IG) will be performed in a sequential order, i.e., initially, all patients that are being admitted to our partner clinic during the first recruitment period will be consecutively assigned to the CG (treatment as usual) until the desired number of cases has been reached. The second recruitment period starts after the recruitment of the CG is completed. Patients that are subsequently arriving at the partner clinic for their MKP will be consecutively assigned to the IG until the desired number of cases has been reached. Neither participants nor the study personnel or care providers at the clinic will be blinded. To control the equal treatment of IG and CG during the MKP, all treatment measures that the groups receive will be continuously documented by means of an EDP-based treatment plan. All patients will complete a written questionnaire using standardized, validated instruments. Table 1 shows the core set of instruments to be used in the study.

**Table 1 Tab1:** Core set of instruments used in the quantitative part of the study

Dimensions	Instruments	t_0_	t_1_	t_2_
Primary Outcome				
Quality of Life	PDQ-8 [24]	●	●	●
Secondary Outcomes				
Participation Restrictions	IMET [24]	●		●
Fear of Falling	FES-I [25]	●	●	●
Sleep Disorder	PDSS-2 [29]	●	●	●
Anxiety/Depression	PHQ-4 [31]	●	●	●
Comorbidity	SCQ-D [26]	●		●
Pain	Single Items [27]		●	
Performance Capability	Single Items [28]	●		●
Physical Activity	Federal Health Survey [29]	●		●
Moderating Variables				
Body Height, Weight	Single Items	●		●
Use of Health Services (Medical and Therapeutic Treatments, Hospital Stays, Medication, etc.)	Single Items	●		●
Sociodemographic Data	Single Items [30]	●		●

t_**0**_ = baseline/right before MKP; t_**1**_ = 3-week follow-up/right after MKP; t_**2**_ = 9 months after t_**1**_

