### Case number calculation / sample size

With regard to the changes in the primary outcome, we assume that both groups (the CG and IG) will have improved in a similar way at the end of the MKP. According to our assumptions, the effect of the CG during the subsequent period will approach the starting level again, while the positive changes in the IG will stabilize or even increase slightly. To estimate the required sample size, we have referred to the results of existing studies on the influence of physical activity on quality of life (PDQ-8) in PD patients. For the effect determination, the data of Ebersbach et al. [46], Morris et al. [47] and Nadeau et al. [10] are being consulted. In Ebersbach et al., the quality of life over a 4-month course showed effect sizes of average magnitude (ES = 0.47) for patients who underwent physical training (Nordic walking), whereas there was no change in the CG. Morris et al. also report a significantly improved quality of life, with a mean effect size of ES = 0.45, after muscle training over a 3-month span. In their controlled study on the effect of intensive treadmill training (speed and incline) on quality of life, Nadeau et al. found an effect size of ES = 0.73 over a 6-month course; for simple treadmill training, they found an effect strength of ES = 0.21. In the CG, the quality of life did not change. For the calculation of the number of cases, we assume that participation in the tablet-based training programme (IG) will lead to clinically relevant positive effects (t_0_ vs. t_2_ ES = 0.40) on quality of life (PDQ-8) 9 months after the end of MKP. In contrast to the IG, there will be no changes in the CG at t_2_. To demonstrate differences between the IG and CG 9 months after MKP on the order of at least ES = 0.4 with two-sided testing at α = 5% and a power of 80%, a group size of *N* = 100 net is required for each IG and CG. We expect only a moderate dropout rate of 25% among patients after MKP due to their attachment to the clinic. Thus, to be able to evaluate N = 100 patients per group, 133 participants per study group must initially be included. Approximately 120 PD patients participate in the MKP per quarter at the partner clinic. Based on the defined inclusion and exclusion criteria, we expect 70 patients per quarter to be included in the study. The recruiting of the CG and IG will take place over a period of nine months each. Taking into account a rate of study refusal of 25%, the targeted number of cases in the clinic can be recruited within this time frame.

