## Limitations

A disease-specific (but rather small) risk is that the disease might deteriorate significantly. In this case, an exercise adjustment will be made in the “negative direction” to ensure that the patient does not feel overwhelmed and can continue training despite deterioration. From a technical point of view, there are risks concerning the possible failure of tablets and the possible breakdown of the data connection in the mobile radio channels. For data transmission, an intelligent mechanism is implemented that repeats transmission attempts in cases of failure after variable time intervals. Because the data are not time-critical, this problem is negligible. In the event of malfunctioning terminal devices, a pool of replacement devices and a strategy for easily transferring the patient-specific settings to the replacement device are maintained. Data security is planned on two stages. In addition to the use of conventional encryption techniques on the data lines, specific encodings of the semantic meaning of the user statistics will be developed that cannot be interpreted by outsiders. Personal data will never be transmitted via a data line. Another risk could arise if changes occur in the structural characteristics of the treated patients after recruitment of the CG is completed. To detect this risk, patient characteristics will be collected and compared for both groups. Existing differences will be adequately included in the analyses (e.g., as covariates in multivariate methods or by propensity score matching). Based on our current knowledge, we assume that the occurrence of such relevant structural changes in the context of the project is unlikely.

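### Recruitment period fixes the arm before consent, so willingness to train can shape who joins the intervention group and can bias the 9-month comparison, probably in its favour

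*Protocol article*

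**What the plan says.** Calendar period alone determines the arm. In the protocol article, section A (quantitative measures), "initially, all patients that are being admitted to our partner clinic during the first recruitment period will be consecutively assigned to the CG", and later "Patients that are subsequently arriving at the partner clinic for their MKP will be consecutively assigned to the IG". The same section states that "Neither participants nor the study personnel or care providers at the clinic will be blinded".

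Under Study design, a physiotherapist at the clinic screens patients in the first three days of the inpatient treatment (MKP). The same person is responsible for "recruiting them into the study by personally addressing potential participants, giving out the information sheet and collecting the informed consent".

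Under Intervention, IG patients receive the tablet at the start of the MKP, attend two seminars and plan a home programme. They then take phone calls and return to the clinic four times. The planned schedule is "at least three 30-min sessions of physiotherapy exercises and for at least one physical activity per week", set for the first three weeks at home and adjusted afterwards. The Abstract describes a 9-month programme for the IG and usual care for the CG. Both groups complete questionnaires.

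The sample size section uses one refusal figure for recruitment: "Taking into account a rate of study refusal of 25" per cent.

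The only safeguard against non-comparable groups is under Limitations. It is framed around the risk that "changes occur in the structural characteristics of the treated patients after recruitment of the CG is completed". Characteristics are to be compared between groups, and any differences found are to enter as covariates or through propensity score matching.

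**The concern.** The recruiter always knows the arm, and IG consent has to cover the tablet programme. A patient with low drive or a dislike of technology can accept the CG offer and decline the IG offer. The Background itself names apathy and anhedonia as frequent obstacles to an active lifestyle.

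Selection of this kind arises even if the clinic's patient population never changes, so it is a different risk from the drift that Limitations describes and considers unlikely. If willingness to train also affects how well quality of life is maintained after discharge, the IG could look better at t2 with no programme effect. A larger sample would not cure this. Willingness that was not asked about before the arm was disclosed cannot be recovered at analysis.

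**Working it through.** **1. The plan's own figures.** Inputs from the sample size section: ES 0.40, two-sided 5%, power 80%, dropout 25%.
- Net n per group = 2 × (1.960 + 0.842)² / 0.40² = 98.1, so 99. The t-test version gives 99.08, so 100. The stated 100 is reproduced, with power of 80.4% to 80.7%.
- Gross n per group = 100 / 0.75 = 133.3; the plan states 133.
- Recruitment: 70 per quarter (read as eligible before refusal) × 3 quarters = 210 per arm. 210 × 0.75 = 157.5 expected consents. The target of 133 is still met with refusal up to 1 − 133/210 = 36.7%. IG refusal could therefore be well above 25% without recruitment falling short.

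**2. Upper case of selection (assumption).** Suppose willingness is normally distributed, the 25% who refuse in the IG period are exactly the least willing quarter, and CG refusal is unrelated to willingness.
- Difference in mean willingness = φ(−0.674) / 0.75 = 0.3178 / 0.75 = 0.424 SD.
- Bias b = r × 0.424, where r is the correlation of willingness with *change* in PDQ-8 from t0 to t2. Change is the relevant quantity because PDQ-8 is measured at t0, the assumed effect is t0 versus t2, and the analysis uses repeated measures. If willingness correlated equally with PDQ-8 at both times, with equal SDs, the bias in change would be zero.

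**3. Partial selection in both arms (assumption).** If refusal correlates 0.50 with willingness in the IG and 0.25 in the CG, the difference is 0.424 × (0.50 − 0.25) = 0.106 SD. With r = 0.3, b = 0.032 SD.

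**4. Consequence with no true effect**, 100 per group: SE = √(2/100) = 0.141, and the false-positive rate is 1 − Φ(1.96 − b/SE) + Φ(−1.96 − b/SE).

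| Case | b (SD) | b / 0.40 | Two-sided false-positive rate |
|---|---|---|---|
| No selection | 0 | 0% | 5.0% |
| Partial, r = 0.3 | 0.032 | 8% | 5.6% |
| Upper case, r = 0.2 | 0.085 | 21% | 9.2% |
| Upper case, r = 0.3 | 0.127 | 32% | 14.6% |
| Upper case, r = 0.4 | 0.169 | 42% | 22.4% |

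The third column assumes that the ES of 0.40 is expressed in the same SD unit as b. The documents give no value for r, for refusal by arm, or for the link between refusal and willingness.

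**5. What the planned adjustment can reach.** Table 1 at t0 includes PDQ-8, physical activity, PHQ-4, performance capability and sociodemographic data. These are partial proxies for drive. No listed instrument asks about intention or motivation to train, although the Intervention section bases the programme on a model centred on forming intentions. As worded, adjustment also depends on differences being observed.

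**The case against.** Several stronger readings are tempting, and the documents do not support them.

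- *IG patients sign up to at least three sessions a week for nine months.* The minimum is stated for the first three weeks at home. It is agreed at the end of the MKP and adjusted later; sessions may be postponed and travel is reimbursed. The contrast in demand is real but smaller than that reading suggests.
- *The home-training exclusion lets the recruiter judge motivation.* It is limited to "cardiovascular and orthopaedic/surgical reasons that argue against independent home training", a medical criterion, and one set of criteria applies to everyone. Applying it in both groups helps comparability. What remains is only that an unblinded person applies it.
- *The driver is unmeasured, so comparing characteristics is useless.* Proxies are collected, and Table 1 is labelled a core set. The action under Limitations covers observed differences whatever their cause. Adjustment may reduce the bias without fully removing it.
- *A fifth to two fifths of the planned effect would be spurious.* That follows only from perfect selection in the IG and none in the CG. CG patients can also refuse, and some of their reasons may overlap with low drive.
- *The single 25% refusal rate asserts equal selection.* It is a feasibility assumption for recruitment.

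The information sheet is also not shown, so what patients are told at consent is inferred. The inference is strong for the IG; what CG patients hear about the programme is unknown.

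These objections limit the size and the certainty. They leave the mechanism standing: the arm is fixed before an open consent process with very unequal demands, and the stated safeguard is written for another risk.

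**Conclusion.** The concern holds as a risk and not as a demonstrated bias. Consent can depend on willingness to train in the IG period, where training is what is offered, and this can bias the 9-month comparison, probably in favour of the IG. The size is not determinable from the protocol. Under the stated assumptions at 25% refusal, it runs from about 0.03 SD (partial selection in both arms, r = 0.3) to 0.08–0.17 SD (upper case, r = 0.2 to 0.4). It is zero if willingness is unrelated to change in PDQ-8. The matter deserves a change before recruitment because the missing information can be collected only at entry.

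**What to change.** Keep the sequential design and make these changes:

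1. Add one or two training-intention items, worded identically in both periods and asked before arm-specific information is given. Use the answers only for patients who then consent.
2. Prespecify these items, together with t0 PDQ-8, physical activity and PHQ-4, as covariates (or in the propensity score) in the primary IG–CG comparison, whether or not an imbalance is observed.
3. Apply the existing exclusion criteria from the same checklist in both periods.
4. Report the numbers eligible and refusing per period; the planned patient-flow file is a natural place to record them.
5. Name residual selection at consent under Limitations, separately from drift in the clinic population.

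The cost is one or two items and slightly more analysis work. Adjustment will reduce the bias but not fully remove it.

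Requiring CG patients to declare themselves willing to follow a hypothetical programme as an inclusion criterion is not advised. Agreeing to a hypothetical programme is not the same as consenting to a real one. The requirement would also narrow the population and could prompt self-started training in the CG.

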### A: quantitative measures

To examine the long-term effects, we will conduct a monocentric, quasi-randomized longitudinal study with three measurement times: at the beginning (t_0_) and end of the MKP (t_1_) and 9 months after the MKP (t_2_). Recruitment of control group (CG) and intervention group (IG) will be performed in a sequential order, i.e., initially, all patients that are being admitted to our partner clinic during the first recruitment period will be consecutively assigned to the CG (treatment as usual) until the desired number of cases has been reached. The second recruitment period starts after the recruitment of the CG is completed. Patients that are subsequently arriving at the partner clinic for their MKP will be consecutively assigned to the IG until the desired number of cases has been reached. Neither participants nor the study personnel or care providers at the clinic will be blinded. To control the equal treatment of IG and CG during the MKP, all treatment measures that the groups receive will be continuously documented by means of an EDP-based treatment plan. All patients will complete a written questionnaire using standardized, validated instruments. Table 1 shows the core set of instruments to be used in the study.

**Table 1 Tab1:** Core set of instruments used in the quantitative part of the study

Dimensions	Instruments	t_0_	t_1_	t_2_
Primary Outcome				
Quality of Life	PDQ-8 [24]	●	●	●
Secondary Outcomes				
Participation Restrictions	IMET [24]	●		●
Fear of Falling	FES-I [25]	●	●	●
Sleep Disorder	PDSS-2 [29]	●	●	●
Anxiety/Depression	PHQ-4 [31]	●	●	●
Comorbidity	SCQ-D [26]	●		●
Pain	Single Items [27]		●	
Performance Capability	Single Items [28]	●		●
Physical Activity	Federal Health Survey [29]	●		●
Moderating Variables				
Body Height, Weight	Single Items	●		●
Use of Health Services (Medical and Therapeutic Treatments, Hospital Stays, Medication, etc.)	Single Items	●		●
Sociodemographic Data	Single Items [30]	●		●

t_**0**_ = baseline/right before MKP; t_**1**_ = 3-week follow-up/right after MKP; t_**2**_ = 9 months after t_**1**_

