#### Secondary outcomes

*Participation restrictions* will be recorded with the IMET. This ICF-oriented [25] instrument determines the subjective impairment of chronically ill people in everyday life. It surveys restrictions on participation in nine everyday areas using a scale from 0 to 10 and can be evaluated both at the individual item level and as a total score. High values indicate high participation restrictions. The IMET has proven valid and reliable for use in chronically ill patients [26, 27].

*Falling anxiety* will be measured with the German version of the Falls Efficacy Scale International Version (FES-I). The questionnaire consists of 16 items rated on a four-point scale, which are combined into a total score. High values indicate high fear of falling. Several studies have reported this instrument’s high reliability and validity [28].

*Sleep problems* will be measured with the German version of the Parkinson’s Disease Sleep Scale (PDSS-2). The scale contains 15 questions rated on a five-point scale that address PD-specific sleep disorders. The items are summarized in a sum scale. High values indicate a high level of sleep disturbances. Reliability and validity can be considered good [29].

To assess *anxiety and depression*, the short version of the Health Questionnaire for Patients (PHQ-4) will be used. The questionnaire captures anxiety and depression with two questions each that are rated on a four-point scale. Sum scores are calculated, and higher values imply higher levels of anxiety and/or depression. Reliability and validity are considered good [30, 31].

*Comorbidity* will be measured by a modified version of the comorbidity questionnaire of Sangha [32], which includes total of 14 diseases that are recorded dichotomously.

The severity of *pain* in different parts of the body will be assessed on a five-point scale [33].

*Performance capability* in the domains of work, everyday life and leisure is quantified using numerical scales from 0 to 10, with high values indicating high performance. The three items have been shown in routine surveys to be a valid method for determining performance limitations [34, 35]. *Physical activity* is measured using the instrument used by Mensink in the 1999 Federal Health Survey [36]. *Sociodemographic data* will be assessed using single items [37].

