
## Statistical methods

### Quantitative analyses

Repeated analysis of variance will be used to analyse the longitudinal data, a contingency table analysis will be used for nominal and ordinal parameters, and chi-square tests and t-tests will be used for subgroup analysis. Subgroup analyses are planned for age, sex and education (boundaries: high vs. low). For the evaluations only complete cases are used. The analyses will be performed using the statistics programme SPSS 22.0.

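### Pain is listed as a secondary outcome but is scheduled only at t1, so neither its change from baseline nor a 9-month group difference can be estimated

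*Protocol article*

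**What the plan says.** All references are to the protocol article.

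- **Section A (quantitative measures), opening.** The purpose and design are given as "To examine the long-term effects, we will conduct a monocentric, quasi-randomized longitudinal study". Assessments are planned at the start of the MKP, at its end, and nine months later. Controls are recruited first, and the intervention group only after control recruitment is complete.
- **Section A, Table 1.** Pain stands under the secondary outcomes with the instrument entry "Single Items [27". It has one mark, in the t1 column; the t0 and t2 cells are empty. The table key defines t1 as "3-week follow-up/right after MKP".
- **Secondary outcomes.** The text says that pain severity "in different parts of the body will be assessed on a five-point scale". It gives no time point, and no other section schedules pain.
- **Quantitative analyses.** "Repeated analysis of variance will be used to analyse the longitudinal data".
- **Case number calculation / sample size.** The target contrast, on the PDQ-8, is at 9 months: "To demonstrate differences between the IG and CG 9 months after MKP on the order of at least ES = 0.4".
- **Limitations.** Patient characteristics will be compared between the groups, and differences will be carried into the analysis, for example as covariates or through propensity score matching.

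**The concern.** The quantitative part is meant to show whether nine months of supported home training has a lasting effect, yet the only scheduled pain value is taken before that phase starts. There is also no pain value from before the MKP. That matters more here than in a randomised trial: the groups come from successive recruitment periods, and the Limitations section itself allows that the patient mix may shift between them. If the published schedule is the one in use, pain cannot answer the question that a secondary outcome of this study is there to answer. A pain value not collected at t0 cannot be recovered later by any analysis plan.

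**Working it through.** The plan gives no figure for pain, so there is none to reproduce; the sample size of 100 per group rests on the PDQ-8. The check is a reading of Table 1, followed by asking which time points each analysis needs.

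**Step 1. Marks in Table 1**

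| Row | Status | t0 | t1 | t2 |
|---|---|---|---|---|
| PDQ-8 | primary | yes | yes | yes |
| IMET | secondary | yes | – | yes |
| FES-I | secondary | yes | yes | yes |
| PDSS-2 | secondary | yes | yes | yes |
| PHQ-4 | secondary | yes | yes | yes |
| Comorbidity | secondary | yes | – | yes |
| **Pain** | **secondary** | **–** | **yes** | **–** |
| Performance capability | secondary | yes | – | yes |
| Physical activity | secondary | yes | – | yes |
| Height/weight, service use, sociodemographics (3 rows) | moderating | yes | – | yes |

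The table has 1 + 8 + 3 = 12 rows. Eleven have both t0 and t2; pain has neither.

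**Step 2. What each pain analysis needs**

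Write Y0, Y1 and Y2 for pain at t0, t1 and t2. Only Y1 is scheduled.

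| Analysis | Needs | Possible? |
|---|---|---|
| Change over the MKP, Y1 − Y0 | t0, t1 | no |
| Change to 9 months, Y2 − Y0 | t0, t2 | no |
| Change over the home phase, Y2 − Y1 | t1, t2 | no |
| Group difference in Y2 | t2 | no |
| Repeated-measures analysis of variance | at least two times | no (one time) |
| Comparison of the groups on baseline pain, or adjustment for it | t0 | no |
| Group difference in Y1 | t1 | yes |

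**Step 3. What the remaining comparison can show**

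The group difference in mean pain at t1 splits into two parts:

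mean Y1 (IG) − mean Y1 (CG) = [difference in mean Y0] + [difference in mean change from t0 to t1]

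Without Y0 the two parts cannot be separated. Covariates that are measured at t0 (PDQ-8, sleep, anxiety/depression, comorbidity, sociodemographic data) can be used for adjustment as the Limitations section foresees, and may remove some of the first part. Baseline pain itself cannot be used. Nothing that happens between t1 and t2 enters the comparison.

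**The case against.** **It may be a misprint.** This is the strongest point. The pain row (empty, marked, empty) is the exact inverse of the t0/t2 pattern in the rows directly above and below it. Table 1 is loose elsewhere too: its citation for pain is 27 where the Secondary outcomes text gives 33, and several other rows disagree with the text in the same way (IMET, FES-I, comorbidity, performance capability, physical activity). The questionnaires are not shown, so t1-only collection cannot be taken as a deliberate choice. This stands and shapes the fix. It does not remove the point: the published schedule then needs correcting, and a single displaced mark could not by itself yield both t0 and t2.

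**A stronger reading.** A reader might infer that the plan expects no group difference in pain at t1, so that a test there would be significant only 5% of the time. The supporting sentence would be "we assume that both groups (the CG and IG) will have improved in a similar way at the end of the MKP". The documents do not support the inference, for three reasons:

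- That sentence opens by limiting itself to changes in the primary outcome, so it says nothing about pain.
- It concerns similar improvement, not equal levels. By the identity in Step 3, equal change still leaves any baseline difference in the t1 comparison, and with sequential recruitment that difference need not be zero.
- t1 is not free of intervention. According to the Intervention section, the intervention group receives the tablet at the start of the MKP and, during it, logs and rates exercises, attends two seminars and plans the home training.

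**It would not be wholly unadjusted.** Correct. The Limitations section allows covariate or propensity adjustment; only adjustment for baseline pain is out of reach.

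**The consequence is small.** Largely correct. Pain appears in neither the aims nor the sample size, and the PDQ-8, measured at all three times, touches on physical discomfort. It is no substitute for pain by body part.

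**Details can be left to the full protocol or SAP.** This does not apply. The article states a schedule, and that schedule conflicts with the status given to the outcome.

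**Conclusion.** The point holds for the schedule as published. For pain, one of eight secondary outcomes, neither change from baseline nor a 9-month group difference can be estimated, the repeated-measures analysis cannot be applied, and baseline pain imbalance between the sequential groups can be neither seen nor adjusted for. A t1 cross-sectional comparison survives, adjustable for other covariates. No expected size or rejection rate for that comparison can be derived from the documents.

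This rests on Table 1 being literally right. If the questionnaires already carry pain at t0 and t2, the fault is only a table error. Either way the primary outcome and its sample size are untouched, so this should be put right but does not threaten the trial's main conclusion.

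**What to change.** 1. Check the pain row of Table 1 against the questionnaires actually issued.
2. If pain is already collected at t0 and t2, correct the table. This costs one line.
3. If it is not, add the existing pain items to the t0 and t2 questionnaires (t1 may stay) and analyse t2 pain adjusted for t0 pain. Both questionnaires are already given, so the cost is a few items and a little more respondent burden.
4. If t0 collection has already passed without pain, relabel pain as a descriptive t1 variable and take it out of the secondary outcomes. Because controls are recruited first, adding t0 pain only once the intervention group starts would leave no control baseline to compare with.

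The check should be made early: the first three options cost little, but a missed t0 value cannot be collected later.
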